### Data analysis plan for the main model

The Difference in Differences approach will be used to compare changes in hypertension and diabetes screening uptake between intervention and control sites over time with a repeated cross-sectional design. A Generalized Estimating Equations model will be utilized as the primary analysis method with site clustered robust standard errors and an appropriate small sample correction to account for the limited number of clusters. In addition, a generalized linear mixed model with a site level random intercept will be used as a sensitivity analysis. Key participant characteristics including age, sex, region of birth, education, primary language, and baseline comorbidities will be included as covariates. Results will be presented as adjusted marginal effects with 95% confidence intervals. Baseline equivalence between intervention and control sites will be examined using standardized mean differences, and any identified imbalances will be controlled for in the modelling. The parallel trends assumption will be assessed indirectly through these baseline comparisons and sensitivity analyses as only one pre intervention time point is available. For secondary outcomes, follow up completion, treatment initiation, and clinical control will be derived from the nested cohort of screen positive individuals and will be summarised and analysed as site period proportions. Missing data will be handled using multiple imputation with additional sensitivity analyses to evaluate the robustness of findings. If individual level data are pooled across sites with fixed per site samples, design weights proportional to the site population of eligible invitees will be used to account for unequal selection probabilities (See Supplementary File 1).

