With regards to the sample size for this quasi-experimental study using the Difference-in-Differences approach, we have considered a hypertension prevalence of 34%, and an assumed baseline screening rate of 50% based on previous literature which shows that only one in two people detected to have hypertension are aware of their condition among the Australian population [4, 5]. Our target is to increase hypertension screening rates among CALD communities from 50% at baseline to at least 70% post-intervention, representing a 20% increase. To detect this difference with 80% power and a 5% significance level, we first calculated the sample size for comparing two independent proportions, assuming individual randomization. This yielded an unadjusted sample size of approximately 182 participants (91 per group).

Nevertheless, given the study’s clustered design involving 12 sites (six intervention and six control clusters), it is necessary to adjust for the expected intra-cluster correlation (ICC), which accounts for the similarity of responses within clusters. This adjustment is done by applying a design effect, calculated as: Design Effect (DE) = 1 + (m − 1) × ICC, where “m” is the average number of participants per cluster. In this study, we expect to recruit 100 participants per cluster and assume an ICC of 0.02 [41]. Applying these values, the design effect becomes: DE = 1 + (100 − 1) × 0.02 = 1 + 99 × 0.02 = 2.98. Applying this yielded an adjusted total sample size of approximately 543 participants, or about 272 per arm. Therefore, with the 100 expected participants from each cluster, the final planned sample size of 1,200 exceeds the minimum requirement and ensures sufficient power to detect the expected effect while remaining practical. Furthermore, the qualitative component will also include in-depth interviews, and stakeholder workshops with CALD communities, healthcare providers, and policymakers to explore perceptions, implementation processes, barriers, and enablers.

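### The sensitivity GLMM has no site-by-period term, so its interval for the difference-in-differences effect is too narrow if site effects shift between rounds; the primary GEE is not affected

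*Protocol article*

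**What the plan says.** In the protocol article, the section Data analysis plan for the main model sets out to "compare changes in hypertension and diabetes screening uptake between intervention and control sites over time with a repeated cross-sectional design". The primary method is a GEE "with site clustered robust standard errors and an appropriate small sample correction to account for the limited number of clusters". The same section then states that "a generalized linear mixed model with a site level random intercept will be used as a sensitivity analysis". It names no other random effect for that model, and it attaches the robust errors and small-sample correction to the GEE only.

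The section Cluster size and number of expected participants gives the design as "12 sites (six intervention and six control clusters)". It also says "we expect to recruit 100 participants per cluster and assume an ICC of 0.02". It gives one ICC and no correlation between a site's results in the two rounds. The planned total is 1,200, and the section does not say whether this is per round or over both.

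**The concern.** The difference-in-differences effect is the mean change in intervention sites minus the mean change in control sites. A site intercept that is the same in both rounds cancels from each site's change, exactly in the balanced linear case and nearly so in a logistic model. The GLMM therefore treats each change as carrying person-level sampling error only. Any site-specific movement between rounds is part of the real error of the effect, and the model sets it to zero.

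The protocol gives reasons to expect such movement:

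- The two rounds need not contain the same people.
- Follow-up comes 6 to 12 months after site activation.
- Phase II allows some components to be fully adapted to local context.
- The process evaluation allows interventions to be changed to suit site needs, so the effect may also vary by site.

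At stake is how much the check is worth. Because there is only one pre-intervention time point, the analysis section says it will rely partly on sensitivity analyses to judge the parallel-trends assumption indirectly. A sensitivity model that rules out site-specific drift gives little help there.

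**Working it through.** **Inputs from the protocol.** Six sites per arm; ICC ρ = 0.02; 100 participants per cluster; screening "from 50% at baseline to at least 70% post-intervention, representing a 20% increase"; 80% power and 5% significance, taken as two-sided.

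**Assumed inputs.** CAC r, from 1 (no shift) down to 0.5. People per site per round, m = 100 if 1,200 is per round and m = 50 if it covers both. Outcome variance 0.25 (a rate of 50%), different people in each round, and no true effect.

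**The plan's own figure.**

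- Per group: (1.96 + 0.842)² × (0.5×0.5 + 0.7×0.3) / 0.20² = 7.85 × 0.46 / 0.04 = 90.3, so 91.
- Design effect: 1 + 99 × 0.02 = 2.98.
- Total: 182 × 2.98 = 542.4.

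The plan states 91, 2.98 and about 543, so its figures reproduce.

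**Variance of the effect.**

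- True: (2/6) × 2 × 0.25 × [(1 − ρ)/m + ρ(1 − r)]
- As seen by the intercept-only model: (2/6) × 2 × 0.25 × (1 − ρr)/m

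The true-to-modelled SE ratio is therefore √{[(1 − ρ) + mρ(1 − r)] / (1 − ρr)}. The actual type I error is 2 × Φ(−1.96/ratio).

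For m = 100 and r = 0.8: (0.98 + 0.40)/0.984 = 1.402, ratio 1.18, type I error 9.8%. For m = 100 and r = 0.5: (0.98 + 1.00)/0.990 = 2.00, ratio 1.41, type I error 16.6%.

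| CAC | SE ratio, m = 50 | Type I, m = 50 | SE ratio, m = 100 | Type I, m = 100 |
|---|---|---|---|---|
| 1 | 1.00 | 5.0% | 1.00 | 5.0% |
| 0.9 | 1.05 | 6.2% | 1.10 | 7.4% |
| 0.8 | 1.10 | 7.3% | 1.18 | 9.8% |
| 0.5 | 1.22 | 10.9% | 1.41 | 16.6% |

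At m = 100 and CAC 0.8 the true SE is 0.0480 and the modelled SE 0.0405. The 95% half-width would be reported as 1.96 × 0.0405 = 7.9 percentage points when it should be 1.96 × 0.0480 = 9.4.

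**Simulation check.** Logistic random-intercept GLMMs were fitted by quadrature to data with no effect (ICC 0.02, 1,000 runs per scenario).

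| CAC | GLMM rejects, m = 50 | GLMM rejects, m = 100 |
|---|---|---|
| 1 | 4.4% | 4.4% |
| 0.8 | 7.6% | 10.7% |
| 0.5 | 11.8% | 15.8% |

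At m = 100 the mean model SE on the log-odds scale was 0.165. The empirical SD was 0.198 at CAC 0.8 and 0.230 at CAC 0.5. A t-test on the 12 site changes rejected 4.0% to 5.8% in the same six scenarios.

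**The case against.** **The primary inference is protected.** This stands. The GEE's corrected robust errors allow for site-by-period variation, and nothing in the document lets the GLMM override the GEE. A reader might infer that the trial's false-positive rate is 10% to 17%, or that the GLMM will falsely confirm the primary result. Neither is supported. The figures above are the GLMM's own rejection rates. False confirmation needs the GEE to be a false positive first, and its corrected test is meant to hold that near 5%. A significant GLMM beside a non-significant GEE would be a visible disagreement, not a confirmation.

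**The narrowing is conditional.** This also stands. At CAC 1 there is none, and the document gives no CAC. A reader might take the intervals to be too narrow whatever happens; the document does not establish that.

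**Overlap of individuals works the other way.** The abstract says only that follow-up data need not come from the same people, so some may appear in both rounds. As an illustration, assume 30% overlap and a within-person correlation of 0.5, which multiplies the person-level term by 1 − 0.3 × 0.5 = 0.85. At CAC 0.8 the type I error falls from 9.8% to about 8.0% (m = 100) and from 7.3% to about 5.6% (m = 50). This shrinks the problem without removing it.

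**Detail may sit in Supplementary File 1.** That file is not shown and could add a correction for the GLMM. But the article itself names the random-effects structure, so this is a stated choice and not an omitted detail.

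**Conclusion.** The point holds in conditional form. If the CAC is below 1, the sensitivity GLMM understates the standard error of the difference-in-differences effect and is a less stringent check than the GEE. At the protocol's ICC of 0.02 and 50 to 100 people per site per round, its nominal 5% test runs at about 6–7% (CAC 0.9), 7–10% (CAC 0.8) or 11–17% (CAC 0.5), and at 5% with CAC 1. These sizes rest on assumed CAC values and on no overlap of individuals.

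The primary estimate, interval and test are unchanged. What is lost is part of the value of a robustness check, in a 12-site non-randomised design that leans on such checks. It is worth correcting because the repair needs no new data.

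**What to change.** Preferred: make the sensitivity analysis a site-level comparison. Compute each site's covariate-adjusted change (follow-up minus baseline) and compare the six intervention sites with the six control sites, using a t reference on 12 − 2 = 10 degrees of freedom. This allows for site-specific shifts without estimating a separate variance component.

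Alternative: keep the GLMM, add a site-by-period random effect, and state a small-sample degrees-of-freedom correction. This is more fragile. An approximate check is the chance that the observed variance of site changes falls below pure sampling variance. At ICC 0.02 and CAC 0.8 this is P(χ²₁₀ < 10 × 0.98/1.38) ≈ 28% for m = 100, and P(χ²₁₀ < 10 × 0.98/1.18) ≈ 40% for m = 50. In those datasets the added variance would be estimated as zero and the fit would return to the intercept-only model. The plan should say what happens then.

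The cost is a wider interval in a secondary analysis. Sample size, data collection and the primary model stay as they are.

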## Methods

### Study design and process

This project will employ a four-phased strategy which has been utilized by other implementation research scholars with each phase focussing on distinct research objectives [22]. A two‑period, before‑and‑after Difference‑in‑Differences design with repeated cross‑sectional sampling at baseline and follow‑up will be utilized to evaluate the impact of the implemented model of care on access to and utilization of hypertension and diabetes screening among CALD communities in Brisbane city. Australia. The Difference-in-Differences approach is a quasi-experimental method that can be utilized to estimate causal effects using observational data when randomization is not feasible. It helps compare the changes in outcomes over time between a treatment group (affected by the intervention) and a control group (not affected) [23–25]. This design is appropriate for our study as it enables comparison of group‑level changes without requiring follow‑up of the same individuals over time. The Exploration, Preparation, Implementation, Sustainment (EPIS) framework will be utilized to guide the phase-wise execution of the overall implementation process of the project work. This framework provides a structured approach to understanding and navigating the complexities of implementing evidence based practices by considering multiple contextual factors [26]. Additional complementary frameworks will also be utilized in different phases depending on the objectives of each phase and other contextual requirements.

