### Cluster size and number of expected participants

We are proposing to include six faith-based organisations having large CALD community followers as intervention sites, as these settings provide trusted community environments that are well suited for delivering an outreach model of care. A matched set of six comparable faith-based organisations will be selected as control sites to allow for meaningful comparison. Faith-based organisations are institutions that are guided by religious principles and provide prayer and other religious activities, as well as services such as social support, education, and healthcare. However, while some of such organizations might focus on specific CALD communities, many may offer services to the wider population regardless of cultural or religious background. Therefore, we are aiming to consider such faith-based settings, and the final selection of which specific organisations to include and not to include will be decided during the later stages of model co-development process, based on relevance and feasibility. All selected organisations will be invited to participate and collaborate throughout the implementation research process, including planning and co-developing the intervention components. Comparability between intervention and control sites will be ensured by selecting organisations with similar CALD population size, demographic characteristics, and levels of community engagement, thereby supporting baseline equivalence across clusters and the assumptions required for a robust Difference-in-Differences approach-based data analysis. The details of the implementation process, including the selection of intervention and control sites, will be determined once the components of the multi-packaged model of care are identified and the model of care is co-developed in consultation with relevant stakeholders.

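### Baseline balance cannot assess parallel trends, and no sensitivity analysis described in the article targets differential drift between arms

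*Protocol article*

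**What the plan says.** The protocol article (Study design and process) fixes the design: "A two‑period, before‑and‑after Difference‑in‑Differences design with repeated cross‑sectional sampling at baseline and follow‑up will be utilized". There is therefore one measurement before implementation and one after, in six intervention and six control sites that are matched but not randomised.

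Under Data analysis plan for the main model, the key assumption is handled in one sentence: "The parallel trends assumption will be assessed indirectly through these baseline comparisons and sensitivity analyses as only one pre intervention time point is available". The comparisons meant are those of the sentence before it: "Baseline equivalence between intervention and control sites will be examined using standardized mean differences, and any identified imbalances will be controlled for in the modelling".

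Two kinds of sensitivity analysis are described in the same section. One is a change of model: "a generalized linear mixed model with a site level random intercept will be used as a sensitivity analysis". The other is attached to incomplete data: "Missing data will be handled using multiple imputation with additional sensitivity analyses to evaluate the robustness of findings".

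Under Cluster size and number of expected participants, sites are to be matched on CALD population size, demographics and community engagement, "thereby supporting baseline equivalence across clusters and the assumptions required for a robust Difference-in-Differences approach-based data analysis". Earlier change in screening uptake is not among the matching criteria. The Limitations section deals with generalisability and representativeness of the settings and does not mention parallel trends.

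**The concern.** A DiD estimate is causal only if, without the programme, both arms would have changed by the same amount. That is a statement about change. A difference in level at baseline is what DiD removes by construction, so showing that levels are similar does not speak to the assumption that remains. The plan nevertheless names the baseline comparison as a means of assessing it, and the site-selection text credits matching with supporting it.

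At stake is how strongly the trial may conclude. If baseline balance is reported as the check, readers will take the effect as better identified than it is, and a secular difference between the two sets of sites could be read as a programme effect.

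**Working it through.** **1. The plan's own figure.** No figure in the article concerns parallel trends. The sample size, whose inputs are reused below, reproduces: (1.960 + 0.842)² × (0.5×0.5 + 0.7×0.3) / 0.20² = 90.3, so 91 per group and 182 in all. The design effect is 1 + 99 × 0.02 = 2.98, and 182 × 2.98 = 542.4, about 543.

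**2. What a baseline comparison can show.** Two constructed examples, both with no programme effect:

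| | Intervention, before → after | Control, before → after | Baseline gap | DiD |
|---|---|---|---|---|
| A | 50% → 60% | 50% → 55% | 0 | (60 − 50) − (55 − 50) = 5 |
| B | 40% → 45% | 50% → 55% | 10 | (45 − 40) − (55 − 50) = 0 |

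A passes the balance check and is biased by 5 points. B fails it and is unbiased. In general, with drift d (the intervention arm's untreated change minus the control arm's), the DiD estimates effect + d, whatever the baseline levels. With one pre-period, d cannot be estimated from the planned data.

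**3. The described sensitivity analyses.** A mixed model with a site random intercept has arm, period and arm-by-period terms plus a constant shift for each site. The shift absorbs level differences, while drift stays in the arm-by-period term, as it does in the primary GEE model. Multiple imputation and its sensitivity analyses vary assumptions about unobserved values, not about trends.

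**4. Covariate adjustment.** The plan says that "any identified imbalances will be controlled for in the modelling" without giving the form. A main effect adjusts level and, in repeated cross-sections, corrects for a change in who is sampled between rounds. It does not let the trend differ by that characteristic. A covariate-by-period term does.

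**5. Size, as an illustration.** From the article: 6 v 6 sites, 100 participants per cluster, ICC 0.02. Assumed:
- the drift;
- 50% uptake in every cell;
- cluster autocorrelation (CAC) between rounds of 0 to 0.8;
- m = 50 to 100 per site and round, which covers reading the 1,200 as both rounds together or as each round;
- a two-sided t test with 10 df.

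Variance of a site-period mean: v = 0.25 × [(1 − 0.02)/m + 0.02]. Covariance between rounds: c = 0.25 × 0.02 × CAC. SE(DiD) = √[4(v − c)/6].

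For m = 100 and CAC 0.5: v = 0.25 × 0.0298 = 0.00745, c = 0.0025, SE = √(4 × 0.00495/6) = 0.0574.

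Chance of rejecting at a nominal 5% with no true effect (non-central t, non-centrality d/SE):

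| m, CAC | SE | d = 5 points | d = 10 points |
|---|---|---|---|
| 50, 0 | 0.0812 | 8.6% | 20.0% |
| 100, 0.5 | 0.0574 | 12.4% | 35.0% |
| 100, 0.8 | 0.0480 | 15.7% | 47.0% |

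**6. What a tipping-point analysis would report.** Suppose the estimate equals the planned 20 points. The SE with 70% in the intervention follow-up cell is 0.0557 (m = 100, CAC 0.5). The lower limit reaches zero at a drift of 0.20 − 2.228 × 0.0557 = 0.076, or 7.6 points. For m = 50, CAC 0 (SE 0.0796) it is 0.20 − 0.177 = 2.3 points. For m = 100, CAC 0.8 (SE 0.0458) it is 0.20 − 0.102 = 9.8 points.

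**The case against.** The article is candid: it calls the assessment indirect, gives the reason and pairs the baseline comparisons with sensitivity analyses. It also refers to Supplementary File 1, which is not shown and may describe more. So a reader might infer that the assumption goes wholly unchecked, and the documents do not establish that. What stands is narrower: nothing described in the article bears on drift, and no supplement can turn a comparison of levels at one time point into a check on trends.

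Balance and matching are not worthless. For a binary outcome, parallel trends depends on the scale, and similar starting levels reduce the conflict between probability and logit scales and make ceiling effects comparable. Matching on demographics and engagement adds plausibility. Main-effect adjustment helps against a shift in sample composition, and the plan does not rule out period interactions.

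A reader might also infer that earlier data are there for the taking. The article does not support this. Reach is the number screened over the number invited, from community registries and screening logs, and registration and invitation belong to Phase III, so the same outcome may not exist for earlier years. The date of a last test would not fill the gap: someone tested last year has an unknown history before that, so uptake in earlier years would be understated. Uptake of one of the cancer screens dropped from scope is a doubtful negative control, because health promotion through community leaders, given as an example of the package, could spill over to it.

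Nor does choosing organisations for relevance and feasibility show that arms were formed on trend. That criterion governs which organisations enter the study, and the matching criteria are stated alongside it.

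Finally, bias equal to drift is a property of every DiD. The defect here is the stated check, not the choice of design.

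**Conclusion.** The point holds in this form: the baseline comparisons cannot assess parallel trends, none of the sensitivity analyses described in the article targets differential drift, and the limitation is not listed. That drift passes one-for-one into the estimate follows from the design and needs no assumption. A 5-point drift would be a quarter of the planned 20-point effect (5/20 = 25%) and, with no true effect, would raise the error rate to about 9% to 16%; 10 points would raise it to about 20% to 47%. The drift and autocorrelation values are assumptions. The documents give neither and do not show that drift of this size is likely between matched sites in one city over 6 to 12 months. The finding therefore concerns how strongly the result may be claimed. It does not show that the estimate will be biased.

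**What to change.** 1. Replace the sentence on parallel trends with a statement that baseline balance and matching lend plausibility to the assumption but do not test it, and add this to Limitations. Bring the site-selection wording into line.
2. Pre-specify a sensitivity analysis that reports the DiD estimate and its confidence interval over a stated range of assumed differential drift, together with the drift that would overturn the conclusion.
3. As a further sensitivity analysis, enter imbalanced covariates with a period interaction as well as main effects. With 12 sites, keep these few.
4. Optional, if feasible: in the baseline round, ask whether the person was tested in each of the preceding years, not only when they were last tested, and run a placebo DiD on the answers. Label it a supportive proxy, subject to recall error and not the Reach outcome.

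Items 1 to 3 need no new data. They cost a little extra analysis and perhaps a more cautious conclusion. Item 4 adds a few survey questions and has to be decided before baseline collection.

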### Outcomes of model implementation

The primary model implementation impact outcome is “Reach”, or the proportion of eligible CALD adults completing hypertension and/or diabetes screening. The primary implementation process outcomes are acceptability, appropriateness, and feasibility of the model of care, measured at the site and stakeholder level. Secondary outcomes include follow-up completion, treatment initiation, clinical control (BP and glycemia), intervention fidelity, program cost, and sustainability. Baseline measurements will be collected prior to implementation, with follow-up assessments occurring at 6 to 12 months post-implementation depending on the specific outcome (See Supplementary File 1). The sustainment component of EPIS framework and the RE-AIM evaluation framework will be utilized to guide assessment of these implementation outcomes related with implementation of the multi-packaged model of care. The RE-AIM framework is a widely used planning and evaluation tool in public health that helps assess the impact and scalability of health interventions across five key dimensions: Reach (the extent to which the target population participates), Effectiveness (the impact on important outcomes), Adoption (the extent to which settings and staff adopt the intervention), Implementation (how well the intervention is delivered as intended), and Maintenance (the extent to which a program is sustained over time) [35]. Originally developed to bridge the gap between research and real-world application, RE-AIM guides both the design and evaluation of programs to ensure they are not only effective in controlled trials but also practical and sustainable in everyday settings. However, some of the implementation outcomes in this study, specifically acceptability, appropriateness, feasibility, fidelity and cost are not native RE-AIM domains. These outcomes are intentionally drawn from Proctor et al.’s taxonomy to complement RE‑AIM’s implementation dimension with complementary measures being mapped pragmatically across the two frameworks [35, 36]. Reach will be calculated as the number screened divided by the number invited within each site and period based on community registries and screening logs. In addition, individuals who screen positive during each measurement period will form a nested cohort for follow up, and these clinical pathway outcomes will be summarised and analysed as site period proportions to remain consistent with the repeated cross-sectional design.

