
### Proposed tools for measuring implementation outcomes

There are various tools that have been utilized to assess various implementation outcomes across the literature. We will be using different adapted tools including the Acceptability of Intervention Measure (AIM), Intervention Appropriateness Measure (IAM), and Feasibility of Intervention Measure (FIM), psychometrically validated tools developed to assess key early-stage implementation outcomes. Each of these instruments consist of four items, rated on a five-point Likert scale from “completely disagree” to “completely agree.” The AIM captures the degree to which stakeholders find an intervention agreeable or satisfactory, making it a useful measure of perceived acceptability. The IAM evaluates whether an intervention is perceived as a good fit or relevant for a given context or problem, thereby assessing its appropriateness. The FIM measures the perceived practicality and ease with which an intervention can be successfully implemented in a specific setting. These tools are designed for ease of use, brevity, and reliability, making them highly suitable for integration into implementation research and practice across diverse settings [37]. In addition, other tools will be utilized depending on the expected outcome measures including the Clinical Sustainability Assessment Tool (CSAT), Short Form, and the Program Sustainability Assessment Tool (PSAT), Short Form, for model implementation sustainability assessment (Table 2).

**Table 2 Tab2:** Implementation outcomes and proposed assessment tools for the model of care

	Constructs	Assessment tools/Measures	Source of data	Method
RE‑AIM Implementation Evaluation Framework with Proctor et al. style implementation outcomes	Reach	Participation rate: % of individuals invited who actually undergo screening for the target NCDs.	Registry lists and clinical records	-
	Effectiveness	Follow-up rate: % of screen-positive individuals who receive timely confirmatory diagnosis and/or treatment.	Clinical records	-
		Proportion of people with controlled hypertension and diabetes among those diagnosed.	Clinical records	-
				-
	Adoption	Proportion of implementing agents/staffs that deliver model of care components.	Clinical records	-
	Implementation			
	✓ Acceptability	Acceptability of Intervention Measure (AIM) 4-items [37].	Implementing site staff members	Survey

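### Follow-up, treatment initiation and control are measured only among people who screened positive or were diagnosed, groups the model is designed to change, so a between-arm comparison mixes better care with a different case mix

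*Protocol article*

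**What the plan says.** Three places in the protocol article fix the denominators.

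- Outcomes of model implementation: "individuals who screen positive during each measurement period will form a nested cohort for follow up". Membership is therefore drawn afresh at baseline and at follow-up. The resulting pathway outcomes are to be analysed as one proportion per site and period, a choice justified there by consistency with the repeated cross-sectional design.
- Data analysis plan for the main model: "follow up completion, treatment initiation, and clinical control will be derived from the nested cohort of screen positive individuals".
- Table 2, Effectiveness rows: the follow-up rate is the percentage "of screen-positive individuals who receive timely confirmatory diagnosis and/or treatment", and control is the "Proportion of people with controlled hypertension and diabetes among those diagnosed".

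The primary impact outcome, Reach, is screening completion, calculated as number screened over number invited in each site and period. The sample-size section states: "Our target is to increase hypertension screening rates among CALD communities from 50% at baseline to at least 70% post-intervention". No version of follow-up, treatment initiation or control per eligible or invited adult is given.

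**The concern.** A person enters the denominator of these secondary outcomes by being screened and found positive (or diagnosed). Getting more people screened is the model's main purpose, so membership of the denominator is itself a result of the intervention. At follow-up the intervention sites' cohort contains people who would not have been screened without the model. The control sites' cohort does not. A difference between arms in the change over time then has two parts: a change in how screen-positive people are cared for, and a change in which people are counted.

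The safeguards that the plan names do not separate the two. Standardised mean differences at baseline look at imbalance before the shift occurs, and a site-period proportion carries no individual covariates. At stake are the Effectiveness measures and the second half of the stated aim, initiation of treatment in those diagnosed.

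**Working it through.** **The plan's own figure first.** For 50% against 70%, with 80% power and a two-sided 5% level (sidedness is my assumption):

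- n per group = (0.50×0.50 + 0.70×0.30) × (1.960 + 0.842)² / 0.20² = 90.3, so 91, or 182 in total.
- Design effect = 1 + 99×0.02 = 2.98, and 182×2.98 = 542.4, so 543.

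Both agree with the sample-size section. The 50% and 70% can be taken as the plan's working values.

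**Inputs from the protocol.** Screening 50% at baseline and 70% after the intervention; hypertension prevalence 34%.

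**Inputs that the protocol does not give (assumed).**

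- Control sites stay at 50% screened with unchanged rates of care.
- Everyone who would be screened without the model is still screened with it.
- Prevalence is the same in newly screened people, and the test is perfect.
- t_old is the success rate (followed up, treated or controlled) in people who would be screened anyway, varied over 60% to 80%. t_new is the rate in those screened only because of the model, varied over 20% to 60% and then 70% to 90%. Lift is the true gain in the first group, 0 or 5 points.

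**Who is in the cohort.** Screen-positives with hypertension per 100 invited:

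- Before: 100×0.50×0.34 = 17.0.
- After, intervention sites: 100×0.70×0.34 = 23.8.
- After, control sites: 17.0.
- Share of the intervention follow-up cohort present only because of the model: 0.20/0.70 = 28.6%.

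**Difference in differences among screen-positives.**

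[0.50×(t_old + lift) + 0.20×t_new]/0.70 − t_old = [0.50×lift + 0.20×(t_new − t_old)]/0.70

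Subtracting the true lift leaves the bias: 0.286 × (t_new − t_old − lift). It is zero only when newly screened people do as well under the model as the others. The estimate is negative whenever t_new < t_old − 2.5×lift.

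**The same people on a fixed denominator.** Among all invited people with hypertension the gain is 0.50×lift + 0.20×t_new. Multiplying by 34 gives people per 100 invited.

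| t_old | t_new | lift | Among screen-positives | Among all invited with hypertension | Per 100 invited |
|---|---|---|---|---|---|
| 70% | 40% | 0 | −8.6 points | +8.0 points | +2.7 |
| 70% | 40% | 5 | −5.0 points | +10.5 points | +3.6 |
| 60% | 60% | 0 | 0.0 points | +12.0 points | +4.1 |
| 60% | 80% | 0 | +5.7 points | +16.0 points | +5.4 |

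**Range.**

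- t_old 60% to 80%, t_new 20% to 60%: among screen-positives, −17.1 to 0.0 points with no lift and −13.6 to +3.6 with a lift of 5. On the fixed denominator, +4.0 to +12.0 and +6.5 to +14.5.
- t_old 60%, t_new 70% to 90%, no lift: +2.9 to +8.6 points among screen-positives, although nothing changed for people who would have been screened anyway.

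**The denominator for control.** The analysis section takes clinical control from the screen-positive cohort, and Table 2 takes it among those diagnosed. A person who screens positive but is not confirmed is in the first denominator and not in the second. The formula applies to Table 2's denominator too, with newly diagnosed in place of newly screened, if diagnosis rises in step with screening.

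**The case against.** The strongest reply is that these are openly defined care-cascade proportions. They are secondary, Reach is reported beside them, and a reader could roughly multiply the two to get a yield per invited adult. The primary analysis is untouched. All of that stands and limits the weight of the point, but it does not remove the selection from a between-arm comparison.

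Four stronger readings are tempting and are not supported.

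- A reader might infer that the plan's difference-in-differences will show harm when the model helps. The article names that method for screening uptake. For these outcomes it says only that site-period proportions will be analysed, so the comparison is implied by the design, not stated. The rates of treatment and control are assumptions, and the bias can vanish or favour the intervention.
- A reader might infer that these analyses are unadjusted. The article does not say so. Individual covariates are lost in a site-period proportion, but adjustment at site level is not excluded.
- A reader might infer that each proportion rests on a handful of people. With 100 invited per site and period, hypertension gives 17 to 24. Diabetes gives 3 to 5 at the national adult figure of 6.6%, but participants are overseas-born and aged 40 or over. At the 12% cited for Bangladesh-born Australians it is 6 to 8. The article does not fix the number invited at 100 either.
- A reader might infer that counting unscreened people as failures solves everything. It does not: care obtained elsewhere is missed, more often in control sites where fewer are screened, which favours the intervention. The measure also rises mechanically with Reach, as the +8.0 points with no lift show.

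**Conclusion.** The point holds as a problem of denominators in the secondary outcomes. At the plan's own target, about 29% of the intervention follow-up cohort would be there only because of the model. Any between-arm comparison over time of proportions within that cohort then carries a bias of 0.286 times the gap between newly screened people and the rest. If newly screened people do worse, the proportion can fall while more people per 100 invited are treated or controlled. If they do better, the proportion rises without better care for the others.

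The 29% rests on the 50% and 70% in the protocol, on stable screening in control sites and on equal prevalence in newly screened people. The sign and size of the bias rest on rates that the protocol does not give. The mismatch between the analysis section and Table 2 on the denominator for control stands on the text alone, unless the analysis section meant the diagnosed subset of the cohort, which it should then say. This should be changed, but it does not threaten the primary result.

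**What to change.** In the data analysis section and Table 2:

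1. For the between-arm comparison of these outcomes, add and put first a version with all invited (eligible) adults in the site and period as denominator, separately for hypertension and diabetes: screened positive and followed up; diagnosed and started on treatment through the programme; diagnosed and controlled. Analyse it with the same difference-in-differences GEE as Reach.
2. Label it as care reached through the programme. State that it partly reflects Reach and does not capture care obtained elsewhere.
3. Keep the proportions among screen-positives and among confirmed diagnoses as descriptive cascade results, without causal interpretation.
4. Reconcile the denominator for clinical control between the analysis section (screen-positive) and Table 2 (diagnosed).

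The cost is low. The registries and screening logs that supply the Reach denominator in every site and period serve here too, and the clinical records supply the numerators, which must be linked to the invitation list. The downsides are smaller absolute percentages and overlap with the primary outcome, so the new measures cannot by themselves show whether care after a positive screen improved.
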